# High-dose intravenously administered iron versus orally administered iron in blood donors with iron deficiency: study protocol for a randomised, controlled trial

**DOI:** 10.1186/s13063-016-1648-y

**Published:** 2016-10-28

**Keywords:** Blood donation, Donor safety, Intravenous iron, Iron carboxymaltose, Iron deficiency, Randomised controlled trial

## Abstract

**Background:**

About 2–3 % of the population participates in blood donation programmes. Each whole blood donation or ten apheresis donations cause a loss of 200–250 mg of iron. As a result, one of the most common risks of regular blood donors is iron deficiency. Although this has been known for decades, in most countries, iron status is currently not assessed or treated in this population. Premenopausal women are particularly affected, as they have lower iron reserves and higher daily requirements. Besides anaemia, iron deficiency may lead to fatigue and impaired cognitive and physical performance. Current iron preparations for intravenous administration are well tolerated and allow for application of large doses up to 1 g in one visit. Our hypothesis is that in blood donors with iron deficiency, intravenously administered iron is more efficient and as safe as oral iron supplementation. Since anaemia is one of the most frequent reasons for permanent or intermittent donor deferral, maintaining an iron-replete donor pool may help to prevent shortages in blood supply and to avoid iron deficiency-related comorbidities.

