**Methods/design:**

In this randomised clinical trial we include male and female blood donors aged ≥18 and ≤65 years with a ferritin value of ≤30 ng/ml. Stratified by gender, participants are randomized with a web-based randomisation tool in a 1:1 ratio to either 1 g of intravenously administered ferric carboxymaltose or 10 g of iron fumarate supplements at one to two daily doses of 100 mg each. Eight to 12 weeks after the first visit, iron status, blood count and symptoms are assessed in both groups. The primary endpoint is the difference in transferrin saturation (%) following the intervention between both groups. Secondary endpoints include other parameters of iron metabolism and red blood cell count, the number of patients with drug-related adverse events, and subjective symptoms including those of the restless legs syndrome, quality of life, and fatigue.

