Several trials have evaluated different regimens of iron supplementation in blood donors and demonstrated good treatment efficacy in improving iron status [13, 16–24]. However, many iron-deficient blood donors may need to permanently take oral iron if they continue to donate frequently, since it typically takes 2–3 months to correct iron deficiency, which is the minimal time interval between whole blood donations. High-dose iron preparations for intravenous administration have become available which allow for the application of a large dose of 1000 mg in one visit, correcting iron deficiency in many individuals with a single infusion [25]. To our knowledge, only two interventional trials using high-dose iron intravenous administration have been performed in blood donors, but only in one study was iron deficiency required for inclusion [26, 27]. Currently, intravenous iron is not routinely accessible to iron-deficient blood donors, and there are no studies that have compared intravenously administered iron to oral iron supplements in this setting. In our study, we aim to establish that intravenous iron is feasible for correction of iatrogenic iron deficiency in blood donors. When costs and logistical impediments are overcome, this could be a one-stop approach if intravenous iron is given immediately after donation through the available venous access.

The potential risks related to iron therapy include the masking of other causes of iron deficiency, iron overload in unrecognized hemochromatosis, and drug-related adverse effects. Results from interventional trials in other settings indicate that severe drug reactions of oral and intravenous iron are rare, and that gastrointestinal side effects are experienced less often with intravenously administered iron than with oral iron supplements [25, 28]. However, anaphylactic reactions have been described in the intravenous administration of iron [29]. A novel, frequent adverse effect after the intravenous infusion of iron and more frequently after ferric carboxymaltose infusion is hypophosphatemia, which may be severe and can lead to profound weakness and even osteomalacia [30–33].

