### Aims and hypothesis of the study

This study will assess the efficacy, safety, and feasibility of intravenous infusion of high-dose iron in blood donors with iron deficiency by comparing intravenously administered ferric carboxymaltose with oral iron fumarate supplements.

Our hypothesis is that 1 g of intravenously infused ferric carboxymaltose will improve the iron status of blood donors with iron deficiency more efficiently compared to a comparable dose of oral iron supplements (10 g assuming a 10 % resorption rate, given over 8–12 weeks).

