#### Secondary objectives

The secondary objectives are:Other parameters of iron metabolism, red blood cell count including the percentage of participants with a normal (gender-specific) haemoglobin at visit 1 (group comparison) and further parameters (e.g. phosphate)Symptoms including those of restless legs syndrome, quality of life, fatigueComparison of the two treatments regarding the incidence and severity of adverse events, tolerance, and compliance

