### Statistical aspects

#### Sample size justification

The sample size calculation was performed by the Department of Medical Informatics, Statistics and Documentation of the Medical University of Graz. Using a two-group *t* test with a 0.05 two-sided significance level, a sample size of 86 participants in each group will have 90 % power to detect a difference in mean of 8 % in transferrin saturation (estimating a post-treatment transferrin saturation of 28 % and 20 % in the high-dose intravenous iron group and oral iron group, respectively, based on results by a similar treatment regimen in otherwise healthy women with postpartum anaemia [34]). Allowing for a dropout of 14 %, originally 200 participants were planned to be enrolled in the study. As the actual dropout rate was substantially lower (<3 %), the study will be terminated after complete study participation of 172 participants plus the number of dropouts.

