#### Statistical procedures

Statistical analyses of the results will be performed using the intention-to-treat and the per-protocol principles. All study participants who are randomised and included into the study will be analysed whether they take their study medication for the entire term (oral iron) or not or whether or not they miss the follow-up visit (visit 1). All primary and secondary outcome measures will be analysed and checked for normal distribution of the results. If there is a normal distribution of laboratory results, they will be analysed by the two-sided *t* test; if there is not a normal distribution they will be analysed by non-parametric tests like the Wilcoxon test for related samples or the Mann-Whitney U test for comparison of independent samples. The significance level will be set to *p* < 0.05. Data will be presented as mean ± standard deviation or median (interquartile ranges) as appropriate. For missing data, no imputation will be performed. A statistical evaluation will be performed using the software program SPSS for Windows (IBM SPSS Inc., Chicago, IL, USA).

A predefined subgroup analysis will separately analyse participants with a baseline ferritin of ≤15 ng/ml. The Department of Blood Group Serology and Transfusion Medicine, Medical University of Graz, will maintain responsibility for the final trial dataset.

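### The abstract hypothesises equal safety of intravenous and oral iron, but the Aims section does not and the plan sets no safety margin, so a non-significant adverse-event comparison could be read as equal safety

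*Protocol article*

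**What the plan says.** The Background part of the abstract gives the trial hypothesis in two halves: "intravenously administered iron is more efficient and as safe as oral iron supplementation". The Methods part of the abstract lists "the number of patients with drug-related adverse events" among the secondary endpoints.

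The main text is narrower. Under Aims and hypothesis of the study, the aim covers safety ("This study will assess the efficacy, safety, and feasibility of intravenous infusion of high-dose iron in blood donors with iron deficiency"), but the hypothesis is that intravenous iron "will improve the iron status of blood donors with iron deficiency more efficiently compared to a comparable dose of oral iron supplements". Nothing is hypothesised there about safety. Under Secondary objectives the two treatments are compared "regarding the incidence and severity of adverse events, tolerance, and compliance", with no criterion attached.

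The Sample size justification rests on "power to detect a difference in mean of 8 % in transferrin saturation", with 86 participants per group at 90 % power and two-sided 0.05. Under Statistical procedures, all primary and secondary outcomes fall within the analysis statement. The tests named there (t, Wilcoxon, Mann-Whitney) are introduced for laboratory results, none is named for adverse-event proportions, and there is one general threshold ("The significance level will be set to" p < 0.05).

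The main-text Background says that anaphylactic reactions have been described with intravenous iron. It also says that hypophosphataemia after infusion is a frequent effect that "may be severe and can lead to profound weakness and even osteomalacia".

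**The concern.** A claim that one treatment is as safe as another needs two things: a statement of how much excess risk would still count as equal, and a result that excludes more than that. The article supplies neither. It states one significance threshold and a sample size justified by a superiority difference in a laboratory value. In that setting, the result most easily offered in support of the abstract's wording is a non-significant difference in adverse events, and that is not evidence of equal safety.

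The participants are healthy donors, and the Discussion looks ahead to giving intravenous iron at donation. A safety conclusion that the data cannot carry would therefore matter.

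**Working it through.** **Inputs.** Per-arm size is 86 (Sample size justification). Total enrolment is 176 (Methods of procedure), or about 88 per arm if the 1:1 allocation came out even. Significance is two-sided 0.05. The article gives no adverse-event rates and says only that severe reactions are rare, so rates of 5 %, 10 % and 20 % are assumed.

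**The plan's own figure.** No standard deviation is stated, so 86 per arm can only be solved backwards. From n = 2(1.960 + 1.282)²·SD²/8² with n = 86, SD = 8·√43/3.242 = 16.2 (16.1 with the exact t distribution). With 14 % dropout, 172/0.86 = 200, as stated. The figure is consistent if the SD is about 16. None of it refers to safety.

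**Precision of the safety comparison.** With a common event rate p, the 95 % half-width for the risk difference is 1.96·√(2p(1−p)/n).

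| Assumed rate | n = 86 | n = 88 |
|---|---|---|
| 5 % | 6.5 points | 6.4 points |
| 10 % | 9.0 points | 8.9 points |
| 20 % | 12.0 points | 11.8 points |

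For example, at 10 %: 1.96·√(0.18/86) = 1.96 × 0.0457 = 0.090.

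**Power of a difference test at 86 per arm.** Power = Φ[(d − 1.96·SE₀)/SE₁], where SE₀ uses the pooled rate and SE₁ the separate rates.
- 10 % v 20 %: SE₀ = 0.0545 and SE₁ = 0.0539, so Φ(−0.125) = 45 % (Fisher's exact test 38 %).
- 5 % v 10 %: SE₀ = 0.0402 and SE₁ = 0.0400, so Φ(−0.718) = 24 % (Fisher's exact test 16 %).

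At these rates a true doubling of risk would be missed more often than found.

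**A worked case.** Take 9/86 events in one arm and 18/86 in the other, an exact doubling. The difference is 10.5 points, with SE = √(p₁(1−p₁)/86 + p₂(1−p₂)/86) = 5.5 points and a 95 % interval from −0.3 to 21.2 points. Fisher's exact p is 0.09. The result is not significant, yet the interval includes an excess of more than 20 points.

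**Severe infusion reactions.** If none occurs in n infusions, the exact two-sided 95 % upper bound is 1 − 0.025^(1/n). This is 4.2 % for n = 86 and 4.1 % for n = 88. The one-sided 95 % bound for n = 86 is 1 − 0.05^(1/86) = 3.4 %.

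**What a margin would require.** The margins here are illustrative, since the article gives none. With equal true rates and one-sided 0.025, power at 86 per arm is Φ[m/√(2p(1−p)/86) − 1.96]. At a 10 % rate this gives 19 % for a 5-point margin, 59 % for a 10-point margin and 91 % for a 15-point margin. For 80 % power with a 10-point margin at that rate, 142 per arm would be needed.

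**Phosphate.** The blood samples described are at visit 0 and at visit 1, 8 to 12 weeks later. A visit-1 value describes phosphate at visit 1. It cannot show whether an earlier fall occurred and recovered.

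**The case against.** The strongest reply is that the equal-safety phrase occurs once, in the abstract. The section that formally states the hypothesis confines it to efficacy, and the Discussion speaks of effectiveness and feasibility. An unpowered secondary safety comparison is not an error. How adverse-event rates are summarised is commonly left to the analysis plan, which is not shown. The article itself expects fewer gastrointestinal effects with intravenous iron, so an excess in that arm is not a given.

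Most of this stands, and it limits the point to a mismatch between a stated claim and the framework that would have to support it. It does not remove the mismatch. The abstract commits to the claim, and nothing else in the article gives it a criterion.

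Three stronger readings are tempting and are not supported:
- **That the plan will treat p ≥ 0.05 as equal safety.** No passage says so. The named tests are for laboratory results and the threshold is a general one, so the misreading is possible but not planned.
- **That half of the trial's hypothesis is untestable.** The hypothesis in the Aims section has no safety half.
- **That the visit schedule misses harmful hypophosphataemia.** The documents give no time course for phosphate, and Data and safety monitoring asks participants to report possible adverse events promptly by telephone, which gives symptomatic events a route. What remains is that an earlier fall without symptoms would not be seen.

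**Conclusion.** The point holds as a mismatch between the abstract and the Aims section, with a practical consequence for what may be concluded on safety. With 86 to 88 per arm, a non-significant comparison leaves a margin of roughly 6.5 to 12 points either side of the estimate, and an absence of severe reactions leaves a risk of up to about 4 %.

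The interval widths and power figures rest on assumed event rates of 5 % to 20 %, and the 88 assumes an even split of the 176 enrolled. The bound for zero events depends only on the number infused. The point is of moderate weight: safety is secondary, and the transferrin saturation analysis is untouched.

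**What to change.** 1. Reconcile the abstract with the Aims section by removing the equal-safety wording, and state safety as an estimation objective. If the published abstract can no longer be changed, record this in the analysis plan before the data are analysed and carry it into the results report.
2. Report the risk difference in drug-related adverse events with its 95 % confidence interval, and the exact upper bound for severe infusion reactions.
3. State that p ≥ 0.05 will not be interpreted as equal safety.
4. If the equal-safety claim is kept, fix and justify a margin before the data are analysed and judge the confidence interval against it. Recruitment is complete, so the margin cannot influence the sample size, and power may be modest.
5. Do not offer a normal visit-1 phosphate as evidence that no earlier fall occurred.

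The cost is a change of wording, a few intervals and a weaker safety claim. No new data are needed.

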**Methods/design:**

In this randomised clinical trial we include male and female blood donors aged ≥18 and ≤65 years with a ferritin value of ≤30 ng/ml. Stratified by gender, participants are randomized with a web-based randomisation tool in a 1:1 ratio to either 1 g of intravenously administered ferric carboxymaltose or 10 g of iron fumarate supplements at one to two daily doses of 100 mg each. Eight to 12 weeks after the first visit, iron status, blood count and symptoms are assessed in both groups. The primary endpoint is the difference in transferrin saturation (%) following the intervention between both groups. Secondary endpoints include other parameters of iron metabolism and red blood cell count, the number of patients with drug-related adverse events, and subjective symptoms including those of the restless legs syndrome, quality of life, and fatigue.

**Discussion:**

Iron supplementation administered intravenously in non-anaemic but iron-deficient blood donors could represent an effective strategy to protect blood donors from comorbidities related with iron deficiency and therefore improve blood donor wellbeing. Furthermore, iron supplementation will help to maintain an iron-replete blood donor pool.

**Trial registration:**

EudraCT: 2013-000327-14, Clinical Trials Identifier: NCT01787526. Registered on 6 February 2013.

**Electronic supplementary material:**

The online version of this article (doi:10.1186/s13063-016-1648-y) contains supplementary material, which is available to authorized users.

## Background

Iron deficiency is possibly the most prevalent nutritional deficiency worldwide, but guidelines for its diagnosis and treatment vary in their suggestions [1, 2]. The largest part of iron is bound to haemoglobin in red blood cells [1]. Each whole blood donation (plus additional samples for testing) causes an iron loss of 200 to 300 mg [3]. Therefore, iron deficiency is prevalent among healthy blood donors, who represent up to 2–3 % of the population [4–10]. Contributing risk factors for iron deficiency include donation frequency, low body weight, and female gender [6, 8, 9]. Traditionally, safety issues in transfusion medicine have been concentrating on product quality and patient safety. However, there is still room for optimizing donor care [11]. In Austria, the maximal annual donation frequency for whole blood donations is 4 times for premenopausal women, 5 times for postmenopausal women and 6 times for men. The maximal annual donation frequency for platelet apheresis is 26 times and for plasmapheresis 50 times [12]. Recently, it has been shown that without iron supplementation, whole blood donors do not recover their predonation hemoglobin and iron status within 6 months [13]. Iron depletion in blood donors has been recognized for decades [14], and anaemia is routinely assessed by point-of-care haemoglobin devices, but iron status is not. Therefore, non-anaemic iron-deficient donors may not be identified, as iron deficiency may lead to subtle and unspecific symptoms [15].

Several trials have evaluated different regimens of iron supplementation in blood donors and demonstrated good treatment efficacy in improving iron status [13, 16–24]. However, many iron-deficient blood donors may need to permanently take oral iron if they continue to donate frequently, since it typically takes 2–3 months to correct iron deficiency, which is the minimal time interval between whole blood donations. High-dose iron preparations for intravenous administration have become available which allow for the application of a large dose of 1000 mg in one visit, correcting iron deficiency in many individuals with a single infusion [25]. To our knowledge, only two interventional trials using high-dose iron intravenous administration have been performed in blood donors, but only in one study was iron deficiency required for inclusion [26, 27]. Currently, intravenous iron is not routinely accessible to iron-deficient blood donors, and there are no studies that have compared intravenously administered iron to oral iron supplements in this setting. In our study, we aim to establish that intravenous iron is feasible for correction of iatrogenic iron deficiency in blood donors. When costs and logistical impediments are overcome, this could be a one-stop approach if intravenous iron is given immediately after donation through the available venous access.

The potential risks related to iron therapy include the masking of other causes of iron deficiency, iron overload in unrecognized hemochromatosis, and drug-related adverse effects. Results from interventional trials in other settings indicate that severe drug reactions of oral and intravenous iron are rare, and that gastrointestinal side effects are experienced less often with intravenously administered iron than with oral iron supplements [25, 28]. However, anaphylactic reactions have been described in the intravenous administration of iron [29]. A novel, frequent adverse effect after the intravenous infusion of iron and more frequently after ferric carboxymaltose infusion is hypophosphatemia, which may be severe and can lead to profound weakness and even osteomalacia [30–33].

### Aims and hypothesis of the study

This study will assess the efficacy, safety, and feasibility of intravenous infusion of high-dose iron in blood donors with iron deficiency by comparing intravenously administered ferric carboxymaltose with oral iron fumarate supplements.

Our hypothesis is that 1 g of intravenously infused ferric carboxymaltose will improve the iron status of blood donors with iron deficiency more efficiently compared to a comparable dose of oral iron supplements (10 g assuming a 10 % resorption rate, given over 8–12 weeks).

## Methods/design

A SPIRIT checklist is available online for this manuscript (Additional file 1).

### Study design

This is a prospective, randomised, clinical trial. The study population consists of healthy adults, including male and female whole blood and platelet apheresis donors with iron deficiency (ferritin ≤ 30 ng/ml).

### Participants

#### Inclusion criteria

The inclusion criteria are as follows:Age ≥ 18 years and ≤ 65 yearsIron deficiency (ferritin ≤30 ng/ml at screening — usually before blood donation)Fulfilment of the Austrian criteria for blood donation

#### Exclusion criteria

The exclusion criteria are as follows:Known haemochromatosisAcute infectionPregnancy or lactationHistory of anaphylaxis to intravenous infusion of iron or other substancesSigns or symptoms suggestive of acute or chronic gastrointestinal or excessive gynaecological bleeding

### Study drugs/intervention

The study drugs used in the intervention are:
**High-dose (1000 mg) intravenous infusions of iron** (ferric carboxymaltose, Ferinject ®, manufacturer Vifor Pharma, Austria) or
**Oral supplements of iron** (iron fumarate, Ferretab®, manufacturer Gerot Lannach, Austria) in a corresponding estimated dose of >10.000 mg (assuming an absorption of 10 %, 100 capsules of 152 mg iron fumarate each) taken over 8–12 weeks. Participants are advised to take tablets in the morning with orange or lemon juice.

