#### Medication

According to the randomization, either 100 tablets of oral iron supplements are handed out to the participant or iron is administered intravenously by the study investigators in the presence of a nurse.

For oral iron supplements, all participants receive an exact schedule for tablet intake together with clear instructions according to the package leaflet: we suggest to take 10 tablets per week (3 days 2 tablets, 4 days 1 tablet) and to take the tablets with orange juice.

Iron is administered intravenously to the participants in a bed in a separate room of the Apheresis Unit of the University Clinic of Blood Group Serology and Transfusion Medicine. Iron is infused intravenously over 30 minutes or more over a dedicated peripheral line. A standard operating procedure involving the resuscitation outreach team of the Department of Anesthesiology has been developed, and basic emergency equipment is available at all times.

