### Visit 1 (8–12 weeks after visit 0)

A treatment period of 8–12 weeks is chosen because the administration of 8–13 doses of 100 mg iron in one week is feasible and it also matches the typical donation interval. Furthermore, serum ferritin levels are falsely high when analysed ≤6 weeks after intravenous infusion of iron.

A CRF including assessment of compliance is completed by the donor, and a blood sample (~30 ml) is drawn. All results are summarized in a written report for the study participants and sent by regular mail.

The CRF at visit 1 will additionally include questions on the following aspects:Information on any relevant adverse events, serious adverse events and adverse drug reactionsCompliance with oral study medication intake (self-reported; the participants are also asked to bring back all leftover medication)

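### The stated capsule strength (152 mg iron fumarate) does not fit 100 mg iron per dose and 10 g in total, so the claim of a comparable oral dose cannot be verified

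*Protocol article*

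**What the plan says.** The protocol article describes the oral dose in five places.

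- **Study drugs/intervention:** the oral arm receives "100 capsules of 152 mg iron fumarate each", presented "in a corresponding estimated dose of >10.000 mg" at an assumed absorption of 10 %, against 1000 mg of iron infused.
- **Aims and hypothesis of the study:** infused iron is expected to do better than a "comparable dose of oral iron supplements (10 g assuming a 10 % resorption rate, given over 8–12 weeks".
- **Medication:** "either 100 tablets of oral iron supplements are handed out to the participant", with a suggested schedule of 10 tablets a week.
- **Visit 1:** the length of the treatment period is justified because "the administration of 8–13 doses of 100 mg iron in one week is feasible".
- **Abstract, Methods/design:** "10 g of iron fumarate supplements at one to two daily doses of 100 mg each".

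No section converts the salt to elemental iron, and no single sentence states the elemental iron in one capsule.

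**The concern.** The infused dose is 1 g of iron. The oral dose is called comparable only because 10 g at 10 % absorption also gives 1 g. That step needs 10 g of *iron*, and so 100 mg of iron in each of 100 units. The intervention section instead gives the unit as 152 mg of a salt, of which iron is only a part. The Abstract adds to the doubt by attaching both the 10 g and the 100 mg to iron fumarate rather than to iron.

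What is at stake is how the primary result is read. If the planned absorbed oral dose is well below 1 g, a higher transferrin saturation after infusion could partly reflect more iron rather than the route. If it is well above 1 g, a small difference could partly reflect the larger oral dose.

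**Working it through.** **Inputs from the article**

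- Units handed out: 100 (Study drugs/intervention; Medication)
- Iron per dose: 100 mg (Visit 1)
- Stated total: 10 g (Aims and hypothesis)
- Absorption: 10 % (Aims and hypothesis; Study drugs/intervention)
- Capsule content: 152 mg iron fumarate (Study drugs/intervention)
- Infused dose: 1000 mg iron (Study drugs/intervention)

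**Assumption, not in the article: iron fraction of the salt**

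- Ferrous fumarate: 55.845 / (55.845 + 114.056) = 32.9 %
- Ferric fumarate, taken as the lower bound: 111.69 / (111.69 + 342.17) = 24.6 %
- Upper bound taken: 35 %

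**Step 1. Reproduce the plan's own figure.** 100 × 100 mg = 10,000 mg = 10 g, and 10 g × 0.10 = 1.0 g absorbed, equal to the infused dose. This uses only the 100 mg iron figure.

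**Step 2. Is one tablet one dose?** 100 tablets over 12 weeks is 100/12 = 8.3 a week, and over 8 weeks 100/8 = 12.5 a week. That matches the 8–13 weekly doses under Visit 1, so each tablet must carry 100 mg iron.

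**Step 3. Test the capsule strength.** 100 mg iron from 152 mg salt needs an iron fraction of 100/152 = 65.8 %. That is twice 32.9 %, and nothing between 24.6 % and 35 % reaches it.

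**Step 4. What each reading implies.** Total = 100 × mg iron per capsule; absorbed = total × 0.10; absorption needed to match = 1 g / total.

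| Reading | Iron per capsule | Total iron | Absorbed at 10 % | Absorption needed for 1 g |
|---|---|---|---|---|
| (a) 152 mg is the salt, 32.9 % iron (range 24.6–35 %) | 50.0 mg (37.4–53.2) | 5.00 g (3.74–5.32) | 0.50 g (0.37–0.53) | 20.0 % (18.8–26.7) |
| (b) 100 mg iron per capsule | 100 mg | 10 g | 1.0 g | 10 % |
| (c) 152 mg is elemental iron | 152 mg | 15.2 g | 1.52 g | 6.6 % |

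**Step 5. Other ways to reconcile the figures.**

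- *Two capsules per dose.* 2 × 152 = 304 mg salt does hold about 100 mg iron (304 × 0.329 = 100). But 100 such doses need 200 capsules, and both sections that give a count say 100.
- *The total read as salt.* 100 × 152 mg = 15.2 g does exceed 10,000 mg. But the absorption rate and the infused comparator refer to iron, and Visit 1 names iron explicitly.
- *The Abstract taken literally, 10 g of salt in 100 mg doses.* 10 g × 0.329 = 3.3 g iron, 0.33 g absorbed. This still conflicts with 152 mg per capsule.

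None of these reconciles the figures.

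**The case against.** The strongest reply is that the article has one coherent set of figures (100 tablets, 100 mg iron, 10 g, 1 g absorbed) and one outlier in a parenthesis. If 152 mg is a misprint or a wrong strength, comparability is intact. This is possible, and it is reading (b). But the document cannot establish it, because the outlier is the only place that states what a capsule contains.

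Second, reading (c) has little textual support, since the text says iron fumarate and not iron. That is fair. It is shown only for completeness, and the realistic choice is between (a) and (b).

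Third, the size of the shortfall depends on an iron fraction that the article does not give, and on 152 mg being the true strength. Both conditions stand. The conflict itself does not depend on the exact fraction.

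Fourth, comparability is approximate in any case because it rests on an assumed absorption rate, and the general aim already compares two treatments without claiming equal dose. This is true of the general aim. The hypothesis, however, does rely on a comparable dose, and a factor of two is more than rounding.

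Last, what participants received follows from the named product and the tablet count, not from the printed milligrams, and the endpoint, sample size and tests do not use the dose. This is correct, and it limits the point to description and interpretation.

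**Conclusion.** The concern holds. As written, 100 capsules of 152 mg iron fumarate cannot supply 100 mg iron per dose and 10 g in total. The salt would have to be 65.8 % iron, against about 33 % by stoichiometry. The planned absorbed oral dose is therefore about half the infused dose (0.50 g, range 0.37–0.53 g) if the capsule strength is right, or equal to it if the 100 mg iron figure is right. The less likely reading of 152 mg as elemental iron gives about 1.5 times.

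All of these use the plan's own 10 % absorption, and the first also uses the assumed iron fraction. The inconsistency is certain; an actual shortfall in dose is not shown. It should be corrected because the hypothesis rests on dose comparability. If the capsule strength is right, the error runs in the direction that favours infusion. The primary test and the sample size are unaffected.

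**What to change.** Check the product label and state the elemental iron per capsule once, under Study drugs/intervention. Bring the Abstract, Aims and hypothesis, Study drugs/intervention and Visit 1 into line with that figure, writing iron where iron is meant and iron fumarate only for the salt. Recompute the planned total and the amount absorbed at 10 %.

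Keep the claim of a comparable dose in the hypothesis and interpretation only if the corrected figure supports it. If it does not, state the actual dose ratio and interpret the primary result as a comparison of two regimens, not of two routes at equal dose.

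The cost is a label check and a wording correction. Recruitment is complete, so the regimen cannot change, but no new data are needed and the primary test and sample size stay as they are. The downside is that the claim of dose equivalence may have to be weakened.
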